#### Datasets

For the analysis, the following datasets for specific populations have been defined: safety set (SAF), which corresponds to all study volunteers who undergo MammoWave examination; full analysis set (FAS), which includes all volunteers who undergo MammoWave examination and have an evaluable result for the primary endpoint and per-protocol set (PPS), which includes all volunteers who do not have significant CIP violations that regard inclusion/exclusion criteria or that can condition efficacy evaluations.

The primary analyses on both primary and secondary outcomes (except safety evaluation) will be performed on the FAS. The analyses on the PP population will be performed if the PP population differs from the FAS by at least 5% and will be considered supportive of the analyses on the FAS population (sensitivity analysis). The safety and tolerability analyses will be performed on the SAF.

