Evaluation of the sensitivity of MammoWave in detecting BC according to the American College of Radiology (ACR) BI-RADS classification.^37^Evaluation of the effectiveness of MammoWave versus a conventional reading of digital mammographic images (either 2D or tomosynthesis) and analysis of whether they are equivalent in terms of detection rates of BC (sensitivity),the number of recalls and positive predictive value (for the biopsies performed).Evaluation of the detection rate (sensitivity) of each system according to the type of mammographic radiological finding (microcalcification, mass, asymmetry or architectural distortion group).Evaluation of the impact of breast density (according to the ACR BI-RADS classification^37^ assigned by the radiologist, with or without automatic software if available) on the MammoWave detection rate of BC, number of recalls and positive predictive value (of the biopsies performed).Evaluation of the impact of breast density (according to BI-RADS classification assigned by the radiologist^37^) on the detection rate (sensitivity) of each system depending on the type of finding (microcalcification, mass, asymmetry or architectural distortion group).Comparison of radiological, histological and stage characteristics between the BCs detected by each system.Evaluation of the reproducibility of the AI-based MammoWave software’s results.Evaluation of the improvement in both sensitivity and specificity when retrospectively using AI algorithms to evaluate MammoWave data after its further optimisation with all the data collected in the patients included in the study.Volunteers’ satisfaction related to MammoWave use, through a properly designed questionnaire (given here as online supplemental material), collecting women’s issues during the exam with MammoWave in the language spoken by the women.

Additionally, there is a secondary objective, which is related to MammoWave safety and tolerability assessment. Furthermore, an additional exploratory objective of the clinical study is to establish a predictive model capable of discriminating and classifying lesions in MammoWave outcomes for volunteers with breast lesions, if feasible.

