
#### Study outcomes

The primary outcomes will be measured as follows:

MammoWave’s sensitivity (percentage of ‘true positive’ results) while using an optimised AI-based classification algorithm.MammoWave specificity (percentage of ‘true negative’ results) while using an optimised AI-based classification algorithm.

The secondary outcomes will be measured as follows:

BC detection rates of each system by type of lesion (microcalcification, mass, asymmetry or architectural distortion group).BC detection rates, recall and positive predictive value (biopsy) of each system, also by breast density (types A and B being low-density breasts (fat), C and D high-density breasts (high content of fibroglandular tissue)).BC detection rates of each system by BI-RADS classification.^37^BC detection rates of each system by type of lesion (microcalcification, mass, asymmetry or architectural distortion group) and density (fat or high content of fibroglandular tissue).Programme screening rate, calculated as the proportion of women diagnosed with BC in the study population.BC detection rates of each system by histological type and size of the BC and BI-RADS classification.^37^MammoWave’s AI classification algorithm’s sensitivity (frequency of ‘true positive’ results) and specificity (frequency of ‘true negative’ results) after a retrospective adjustment using the data at the end of the study.BC detection rate, recalls and positive predictive value (biopsy), also by breast density (types A and B or C and D) after retrospective AI adjustment using the data at the end of the study.Programme screening rate, calculated as the proportion of women diagnosed with BC in the study population after a retrospective adjustment using the data at the end of the study.Evaluation of the reproducibility of results comparing the lectures performed at the study centres and the centralised lectures.Volunteers’ satisfaction through a properly designed questionnaire collecting women’s issues during the exam with MammoWave in the language spoken by the women.

Regarding safety outcomes, all the events will be registered, and they will be identified as related or not to MammoWave.

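### The satisfaction questionnaire falls under the FAS rule, so examined women without an evaluable accuracy result drop out of a patient-experience outcome

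*Protocol article*

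**What the plan says.** Three parts of the protocol article bear on this.

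- **Study outcomes.** The last entry in the list of secondary outcomes is the volunteers' "satisfaction through a properly designed questionnaire collecting" the problems women had during the exam. Safety comes after the list, in its own sentence: "Regarding safety outcomes, all the events will be registered, and they will be identified as related or not to MammoWave".
- **Hypothesis and objectives.** The split is the same. Satisfaction closes the list of secondary objectives, and the text then adds: "Additionally, there is a secondary objective, which is related to MammoWave safety and tolerability assessment".
- **Datasets.** The two relevant sets are the "safety set (SAF), which corresponds to all study volunteers who undergo MammoWave examination" and the "full analysis set (FAS), which includes all volunteers who undergo MammoWave examination and have an evaluable result for the primary endpoint". They are then assigned by two rules: "The primary analyses on both primary and secondary outcomes (except safety evaluation) will be performed on the FAS", and "The safety and tolerability analyses will be performed on the SAF".

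No section says which variables make up tolerability, or whether the questionnaire is one of them.

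**The concern.** An evaluable result for the primary endpoint is a sensible entry condition for sensitivity and specificity. It has no bearing on whether a woman can report what the exam was like. Applied to the questionnaire, it can remove two kinds of examined women.

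1. **Women with no usable MammoWave label because the scan was stopped or failed.** The exam is done lying face down and takes 8 minutes per breast (MammoWave device and imaging algorithm). A woman who could not manage this is one whose answers matter most, and leaving her out would tend to make satisfaction look better than it was.
2. **Women with a label but no adequate reference result.** The reference standard includes 2 years of follow-up (Abstract; Follow-up). A woman lost in that period may have no evaluable accuracy result, although her view of the exam was already formed. Leaving her out wastes data without any obvious direction of bias.

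The full study title in The clinical study section presents the technology as friendly to women, and the questionnaire is the outcome that would most directly support that description.

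**Working it through.** The plan gives no figure on this point to reproduce, so the check is mainly a reading of the rules against the outcome list.

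**Step 1: which rule reaches the questionnaire?**

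| Item | Where listed | Rule in Datasets | Set |
|---|---|---|---|
| Sensitivity, specificity | Primary outcomes | Primary and secondary outcomes | FAS |
| Satisfaction questionnaire | Secondary outcomes, last entry | Secondary outcomes other than safety evaluation | FAS |
| Adverse events | Separate safety sentence | Safety and tolerability | SAF |
| Tolerability | Separate secondary objective; no variable named | Safety and tolerability | SAF |

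The questionnaire is on the secondary list and is not described as safety, so the literal reading sends it to the FAS.

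**Step 2: who is in the SAF but not in the FAS?** The definitions differ by one condition, the evaluable primary-endpoint result. That result needs both a MammoWave label and a reference classification, so lacking either could exclude a woman. The article does not say how a stopped scan or a scan of one breast is classed. Nor does it say whether a woman who stops counts as having undergone the exam.

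**Step 3: would those women have questionnaire data?** Data collection, management and monitoring says that volunteers are given the questionnaire and does not limit this to completed exams. It does not confirm that women who stop will fill it in.

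**Step 4: size.** Let f be the share of SAF women not in the FAS, s_F the proportion satisfied in the FAS, and s_X the proportion satisfied among those left out.

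- Proportion satisfied in the SAF = (1 − f)·s_F + f·s_X
- Overstatement by the FAS = s_F − [(1 − f)·s_F + f·s_X] = f·(s_F − s_X)

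The article gives none of these three inputs. The gap between the maximum of 10 000 and the minimum of 8000 participants (Number of participants) is not described as an allowance for non-evaluable exams, so it does not supply f. The values below are assumptions, with s_F = 90%.

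| f (assumed) | s_X = 50% | s_X = 10% |
|---|---|---|
| 1% | 0.01 × 40 = 0.4 points | 0.01 × 80 = 0.8 points |
| 5% | 0.05 × 40 = 2.0 points | 0.05 × 80 = 4.0 points |
| 10% | 0.10 × 40 = 4.0 points | 0.10 × 80 = 8.0 points |

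If the women left out lack only a reference result and answer like everyone else, s_X = s_F and the overstatement is zero whatever f is. Only exclusions linked to the exam itself create bias.

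**The case against.** The strongest reply is that Datasets already puts tolerability on the SAF. If the questionnaire measures tolerability, it is covered. If it does not, the FAS rule applies and tolerability is untouched. A reader might infer from the FAS rule that tolerability will be overstated, or that the questionnaire is the only evidence on how women bear the exam. The document supports neither reading. Adverse events are a collected variable, recorded from consent until data acquisition ends, with severity, relatedness and action taken, and they belong to the safety analyses on the SAF. This part of the reply stands and limits the point to satisfaction. It does not remove the point: the questionnaire is listed as a secondary outcome and is nowhere called a tolerability measure. Adverse events are also judged by the investigator, so they do not replace the women's own answers.

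A second reply is that the FAS condition is evaluability, not completion. It would go too far to say that the plan discards questionnaires from women who stopped; the article does not say how such exams are classed or whether those women answer. That stands. The exclusion of stopped scans is a possibility, not a stated fact.

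A third reply is that non-evaluable scans may be few. Women too large for the largest cup are excluded beforehand, and the exam involves no compression. That is reasonable, and if they are few the bias is small.

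A fourth reply is that an analysis set for a descriptive questionnaire can be left to the SAP. Here, however, the article states the rule rather than leaving it open, and a SAP that follows it would inherit the FAS.

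**Conclusion.** The point holds for the satisfaction outcome only. As written, the plan analyses the one described patient-reported measure of the exam on a set defined by accuracy evaluability, although a set without that condition is defined in the same section. The consequences are a possible upward bias, if some exclusions come from stopped or failed scans, and some avoidable loss of data, if others come from a missing reference result.

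The size is unknown. The figures of 0.4 to 8 points rest wholly on assumed exclusion and satisfaction rates and show only how the bias scales. The direction rests on the further assumption, plausible but not documented, that women whose scan was stopped or failed were less satisfied and would have answered the questionnaire.

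Satisfaction is a descriptive secondary outcome; the stated hypothesis covers only sensitivity and specificity. No accuracy estimate, sample size or decision rule is affected, so this is a minor improvement.

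**What to change.** In Datasets, add that the satisfaction questionnaire is analysed on the SAF, as an exception to the FAS rule for secondary outcomes. In the same sentence, make explicit whether an exam that was started but not completed counts as having undergone MammoWave. Report the number of uncompleted and of non-evaluable exams beside the satisfaction results, so that a reader can judge how far the two sets differ.

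The cost is close to nil. The SAF is already defined and the questionnaire is already collected. The one substantive decision is how to treat exams that were started and stopped. Because it also settles the denominator for the safety analyses, it should be made once and applied to both.

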### Analysis

#### Number of participants

The maximum number of participants will be 10 000 (for all the sites). The sample size was determined using the Buderer approach,^40^ considering that (1) the primary objective of the study is to confirm that MammoWave reaches sensitivity >75% and specificity >90% in BC detection on 10 000 volunteers undergoing breast screening, (2) a two-tailed 95% CI for sensitivity and specificity (CI width=10) and (3) a prevalence of female BC detected due to screening of 0.92%, according to the official English statistics of the National Health Service (NHS) Breast Screening Programme.^41^ A minimum of 8000 participants is required to reach the primary endpoint.

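### The 5% trigger for the supportive per-protocol analysis is counted in all women, so it barely responds to exclusions among the cancers on which sensitivity is estimated

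*Protocol article*

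**What the plan says.** The rule is in the Datasets section of the protocol article.

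- The main set is the "full analysis set (FAS), which includes all volunteers who undergo MammoWave examination and have an evaluable result for the primary endpoint".
- The per-protocol set (PPS) "includes all volunteers who do not have significant CIP violations that regard inclusion/exclusion criteria or that can condition efficacy evaluations".
- Roles: "The primary analyses on both primary and secondary outcomes (except safety evaluation) will be performed on the FAS". The PP results "will be considered supportive of the analyses on the FAS population (sensitivity analysis").
- Trigger: "The analyses on the PP population will be performed if the PP population differs from the FAS by at least 5" per cent. No separate count is given for women with cancer.

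The section on the number of participants sets a ceiling of 10 000 women and a minimum of 8000, and assumes "a prevalence of female BC detected due to screening of 0.92" per cent. Under the choice of comparator, a woman is reference-positive only if histology confirms cancer. Those women alone form the denominator of sensitivity.

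**The concern.** A size trigger for a supportive analysis assumes that the share of participants excluded indicates how far the result could move. That is reasonable when every participant contributes to the estimate. Here sensitivity rests on fewer than 1% of the set and specificity on the rest. One percentage of all women therefore serves two denominators that differ about a hundredfold.

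A handful of exclusions among cancers is negligible as a share of all women but can be a material share of the sensitivity denominator. At stake is whether the report shows how sensitivity behaves without significant violators. Under the stated rule that comparison could be omitted although it would have been informative, and its omission would reflect the number of women without cancer who were excluded.

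**Working it through.** **Inputs from the protocol article.** Maximum N = 10 000, minimum N = 8000, prevalence 0.92%, targets of sensitivity >75% and specificity >90%, 95% confidence and a stated CI width of 10 (Number of participants); trigger 5% (Datasets).

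**Step 1: the plan's own figure.** Buderer: cases = 1.96² × Se × (1 − Se) / W², and N = cases / prevalence.

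- W = 0.10 as half-width: 3.8415 × 0.75 × 0.25 / 0.01 = 72.03 cases; 72.03 / 0.0092 gives N = 7830 (7935 if cases are first rounded up to 73). This agrees with the stated minimum of 8000.
- W = 0.05 (10 points as full width): 288.1 cases, N = 31 317. This does not reproduce 8000.

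The plan's sample size therefore rests on roughly 72 to 92 cancers, with a precision of about ±10 points.

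**Step 2: trigger against cancer count.**

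| N | Exclusions needed (0.05 × N) | Expected cancers (0.0092 × N) | Ratio |
|---|---|---|---|
| 10 000 | 500 | 92 | 5.4 |
| 8000 | 400 | 73.6 | 5.4 |

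The ratio is 0.05 / 0.0092 = 5.43 at any N. As an arithmetic bound, excluding every expected cancer would be 0.92% of women and would leave the trigger 408 exclusions short at N = 10 000 (500 − 92), or about 326 short at N = 8000 (400 − 73.6). Applied to cancers alone, the same 5% would be reached at 5 of 92 (0.05 × 92 = 4.6) or 4 of 74 (0.05 × 73.6 = 3.7).

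**Step 3: possible shift in PP sensitivity.** Assume 69 of 92 cancers detected in the FAS: 75.0% (Wilson 95% CI 65.3 to 82.7). Exclude ten cancers, which is 10 / 10 000 = 0.1% of women:

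| Of the ten excluded | PP sensitivity | Wilson 95% CI |
|---|---|---|
| all detected | 59/82 = 72.0% | 61.4 to 80.5 |
| 8 detected | 61/82 = 74.4% | not calculated |
| 7 detected | 62/82 = 75.6% | not calculated |
| all missed | 69/82 = 84.1% | 74.7 to 90.5 |

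None of these exclusions would bring the trigger appreciably nearer: ten women are one fiftieth of the 500 required.

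**Step 4: exclusions unrelated to cancer status.** Just under 5% of all women excluded at random would remove about 0.0499 × 92 = 4.6 cancers. The trigger is then silent, but little is lost.

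**The case against.** The strongest reply is that nothing decisive depends on this analysis. The FAS is primary, the PPS is supportive, and the interim rule under Statistical considerations does not mention the PPS. This stands: skipping the PP analysis changes neither the primary sensitivity estimate nor its interval. A reader might infer that the sensitivity endpoint itself is compromised; the documents do not support that.

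Second, the large shifts are extremes. They need about 11% of cancers (10 of 92) to be significant violators, and all ten to be missed or all detected. With seven or eight of the ten detected, sensitivity moves by about 0.6 points, and even 72.0% lies inside the FAS interval. This also stands. Loss of every cancer is a bound, not an expectation.

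Third, a reader might infer that violations will cluster in cancers, because a woman with a suspicious mammogram at entry breaches the exclusion for signs of cancer, or because cancers go through more work-up. The text does not establish this. Eligibility admits women whose recent mammogram result is already available, so whether a suspicious reading is a breach is an ambiguity in the criteria. Work-up follows each site's own pathway, and variation in it is not plainly a significant violation. The added ultrasound follows a positive label: at 90% specificity, about 0.10 × 9908 = 991 women without cancer against 69 with it, so omissions would fall mainly among non-cancers.

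Fourth, it would be wrong to say the check is skipped exactly when it matters. The trigger follows total exclusions: it is also silent when violations are few and harmless, and it can fire when cancers are affected.

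Finally, the SAP may add other sensitivity analyses, and the article does not spell out the base of the 5%. But the trigger is a rule stated in the protocol, and both sets are defined in volunteers. None of these replies makes a share of all women a suitable trigger for an outcome estimated in under 1% of them.

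**Conclusion.** The point holds as a weakness in a supportive analysis. The trigger is about 5.4 times the expected number of cancers at either sample size, so it carries almost no information about exclusions in the sensitivity denominator. In the illustration, excluding 0.1% of women gives a PP sensitivity anywhere from 72.0% to 84.1% against 75.0% in the FAS, with almost no shift if detection among those excluded is the same.

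This rests on three assumptions: the 5% is of women, prevalence is near 0.92%, and FAS sensitivity is 69/92 (chosen for illustration). The 0.92% covers screen-detected cancers. Interval cancers over the two-year follow-up would add to the 92, but cancers would have to reach 5% of women before losing all of them could fire the trigger alone. The documents give no forecast of how many cancers will be violators, so the size of any actual shift is unknown.

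**What to change.** Preferred: delete the condition and state that sensitivity and specificity will be estimated in the PPS as well as the FAS whatever the difference in size, as supportive results.

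If a trigger is kept, apply it separately by reference status: PP sensitivity according to exclusions among reference-positive women, and PP specificity according to exclusions among reference-negative women, naming the denominator of each percentage. At 5%, the first would need 5 of 92 cancers, or 4 of 74. Running PP sensitivity when any reference-positive woman is excluded would be close to unconditional and simpler to apply.

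The cost is one sentence in the protocol and SAP and one extra supportive table from data already collected. No additional participants are needed, and the primary analysis is unchanged.

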#### Statistical considerations

Data from study participants will be analysed with descriptive statistics (mean, median SD, IQR, min/max for numerical variables, with frequency tables for categorical ones, percentages), 95% CIs as appropriate and graphical analysis on both the entire population and by strata (ie, dense/no dense breast) at the interim analysis and the end of the study. All the methods adopted for the statistical analyses will be described in the statistical analysis plan (SAP), to be issued before the interim analysis. The SAP will include a dedicated section in which the interim analyses are described. We anticipate that, within the interim analysis, sensitivity and specificity will be evaluated. In case the lower limit of the 95% CI is lower than 60% for the sensitivity or 70% for the specificity, the classification algorithm will be updated; otherwise, the study will continue without any modification.

All analyses will be conducted by using SAS (SAS Institute) V.9.4.

#### Data collection, management and monitoring

During each study visit, the study investigator (or designee) will first collect a written informed consent from the volunteer. All clinical data will be collected, anonymised and properly identified with a dedicated study identification number and stored in an eCRF, secured by the Clinical Research Organisation, CRO (JSB Solutions, Italy). The investigator is responsible for ensuring the accuracy, completeness and consistency of the data entered in the eCRF. The data entered in the eCRF (in English language) must be present in the source documents of the volunteers at the investigational centre.

The investigator and the designated person from his/her staff will be trained by CRO for the use of the eCRF and will be responsible for the data entry into the eCRF in accordance with the relevant user guidelines. During the study, the medical records related to the participating volunteer will be kept in the centre. Source data must be available at the site to document the existence of the study participants.

The eCRF system will record the date and time of any entry and/or correction and the user ID of the person making the entry/correction (audit trail). Only authorised investigators will be allowed to view and use the eCRF. The investigators will review all eCRFs and electronically sign and date them for each subject, verifying that the information is complete, true and correct. All fields on the eCRF must be completed as applicable. Volunteers will be provided with a properly designed questionnaire collecting women’s issues and thoughts during the exam with MammoWave, in the language spoken by the women. A copy of all questionnaires will be stored in the subject’s folder as a source document. It is the responsibility of the investigator to correctly enter the data collected by the questionnaire in the relevant sections of the eCRF.

The collection of AEs will start after the time that the informed consent is signed and continue until the volunteer completes the data acquisition. Investigators must obtain all information available to determine the causality and outcome of the AE and to assess whether it meets the criteria for classification as a serious AE requiring immediate notification to the Sponsor. All reported AEs will be documented on source documents and then reported on the eCRF and will include the event description, date of onset date, resolution, seriousness, severity, relatedness, cause, action taken and outcome. The investigator or an authorised designee must assess the causality, severity and relatedness for all the AEs.

Data will not be shared with any outside person or organisation and will not be used except for the development of this study.

The monitoring activities will be conducted by the CRO according to a monitoring plan agreed with the sponsor. The eCRF pages will be reviewed both on-site, by the monitor of the centre, and remotely, by the Data Management staff of the CRO. Data clarification sheets will be generated through the eCRF system, both automatically, through edit checks, and manually, by clinical research associates (CRAs) and/or data managers; the investigator will have to check and solve them. The CRAs will be permitted to inspect all study documentation provided that subject confidentiality is respected; to verify the patients’ informed consent forms, to verify the data reported in eCRF versus the source data and in case of any discrepancies, they will issue the queries. The corresponding investigator is responsible for the review and approval of all query resolutions. The CRAs will be responsible to verify the proper management of study documentation at the site.

